### Sample size

The number of participants to be included in the study was calculated on the basis of the change in quality of life as assessed with the *EuroQol 5D (*EQ-5D-5 L). To the best of our knowledge, there is no available data regarding group differences in changes in quality of life following any type of intervention in middle aged women. Therefore, we assumed a difference of 0.07 units as clinically meaningful based on previous observations from our group (unpublished observations). Therefore, a total of 124 participants (62 per group) is needed to detect a mean group difference of 0.07 and a standard deviation of 0.12 in the total EQ-5D score with a power of 90 % and α of 0.05. However, we will attempt to exceed this sample size to allow for withdrawals. Assuming a maximum lost-to-follow up of 20 %, a minimum of 75 participants per group will be recruited (*n* = 150).

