### Primary and secondary outcomes

#### Primary outcomes

The Incremental Cost Effectiveness Ratio (ICER) [19]. For each group (intervention and control) an average of cost and health effects will be calculated. The measurement of health effects is defined as the Quality Adjusted Life Years (QALYs). The QALYs are calculated multiplying the years of life by the participants’ quality of life. The participants’ quality of life will be assessed by the EQ-5D-5 L questionnaire. The ICER will be calculated dividing the difference between the average costs of both groups by the difference in mean QALYs gained in both groups [19].$$ \mathrm{ICER}=\frac{\mathrm{Cos}{\mathrm{t}}_{\mathrm{Intervention}}-\mathrm{C}\mathrm{o}\mathrm{s}{\mathrm{t}}_{\mathrm{Control}}}{\mathrm{QAL}{\mathrm{Y}}_{\mathrm{Intervention}}-\mathrm{Q}\mathrm{A}\mathrm{L}{\mathrm{Y}}_{\mathrm{Control}}} $$

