### Statistical analysis

Baseline characteristics of the study participants will be presented as mean (standard deviation) for continuous variables and proportions for categorical variables.

Statistical analysis will be performed on the intention to treat population, thus including all randomized participants (in the groups to which they were randomly assigned) in the analysis. Missing data will be replaced using multiple imputations. The effects of the intervention on the primary and secondary outcomes will be assessed with repeated measures analysis of covariance adjusted for age and baseline values. The effect size (95 % confidence interval) and statistical significance will be reported for each study outcome with regards to the main group (between-subjects) time (within-subjects) and their interaction (group × time) effects. The statistical significance will be set at the conventional level of p<0.05. To account for potential estimations biases or inefficiency, sensitivity analyses will be undertaken using baseline observation carried forward imputation, and also the available case population (participants who actually received the treatment; i.e. no imputations).

*Ancillary analyses.* "Per-protocol" analyses will also be performed on participants with overall ≥75 % treatment compliance.

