#### Cost-effectiveness analysis

A cost-utility analysis with a health system perspective will be conducted in line with the methodological recommendations suggested by Lopez-Bastida et al. [60], and the guidelines defined in the economic evaluation literature [19, 61].

The study will be conducted considering the costs and the health effects of the intervention. Only direct costs of the program will be identified and valued. As direct costs for both groups, the drugs consumption, primary care visits, and hospital admissions will be considered. In the intervention group, the time dedicated by sport professionals of the exercise program will also be considered. Their total remuneration will be calculated based on the collective agreement for these professionals. First, for each group (intervention and control) an average of cost and effectiveness (the mean QALYs gained) will be calculated. Secondly, the ICER [19] will be calculated. To analyse the uncertainty in model parameters and verify the robustness of the ICER, various deterministic and probabilistic sensitivity analyses will be held [62]. The probabilistic analysis will be carried out through bootstrapping non parametric methods with 1000 replications. The resulting 1000 ICER replications will be plotted on the cost-effectiveness plane and will be used to construct an acceptability curve [63]. The cost-effectiveness plane is a graphical way of presenting cost-effectiveness results, with the difference in costs on the vertical axis and the difference in health benefits on the horizontal axis. Since incremental costs and health benefits can both be either positive or negative, there are four possible combinations, which will be reflected in the four quadrants of the cost-effectiveness plane:Upper-left quadrant: intervention less effective and more costly than comparator.Lower-left quadrant: intervention less effective and less costly than comparator.Upper-right quadrant: intervention more effective and more costly than comparator.Lower-right quadrant: intervention more effective and less costly than comparator.

The acceptability curve represents the proportion of simulations in which the intervention was considered cost-effective over a range of values of the threshold cost- per-QALY [64]. All analyses will be conducted in Stata v.13 (Stata Corp, College Station, TX, USA).

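### The planned ANCOVA cannot be fitted to the primary outcome, an ICER, and the plan does not say how a bootstrap replicate is classed as cost-effective for the acceptability curve

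*Protocol article*

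**What the plan says.** Primary outcomes section: the ICER is the sole primary outcome. "The ICER will be calculated dividing the difference between the average costs of both groups by the difference in mean QALYs gained in both groups".

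Statistical analysis section: "The effects of the intervention on the primary and secondary outcomes will be assessed with repeated measures analysis of covariance". Age and the baseline value are to be covariates. An effect size with 95% CI and a significance test are promised for each outcome, for the group, time and group-by-time effects.

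Cost-effectiveness analysis section: the ICER gets a separate non-parametric bootstrap with 1000 replications. "The resulting 1000 ICER replications will be plotted on the cost-effectiveness plane and will be used to construct an acceptability curve". The section describes the plane by its cost and effect axes, lists all four quadrants (including less effective and more costly), and describes the curve as the proportion of simulations judged cost-effective at each threshold. It does not say how a simulation is judged.

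Sample size section: "The number of participants to be included in the study was calculated on the basis of the change in quality of life". The result is that "a total of 124 participants (62 per group) is needed to detect a mean group difference of 0.07 and a standard deviation of 0.12", "with a power of 90 % and α of 0.05".

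**The concern.** There are three linked difficulties, all about the outcome on which the trial's main conclusion rests.

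1. Two analyses are prescribed for the primary outcome, and one is impossible. An ICER has no individual value, no baseline value and no value by visit, so there is nothing to enter into a repeated measures ANCOVA.

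2. The acceptability curve is said to come from ICER replications. A negative ICER can mean that exercise is better and cheaper, or worse and dearer. A low positive ICER is favourable when exercise gains QALYs and unfavourable when it loses them. If replicates were counted simply because the ratio lies below the threshold, bad results would be counted as good. The distortion is largest when the intervention does little, which is when a payer most needs a correct answer.

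3. The 90% power belongs to the EQ-5D-5L difference. A reader who sees one primary outcome and one power statement may attach the second to the first.

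**Working it through.** **The plan's own figure.** Inputs from the Sample size section: difference 0.07, SD 0.12, power 90%, α 0.05 (taken as two-sided).
- n per group = 2 × (1.960 + 1.282)² × (0.12/0.07)² = 61.8, so 62.
- Power at 62 per group = Φ(0.07 / (0.12 × √(2/62)) − 1.960) = 0.901.

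The stated 124 reproduces, for the EQ-5D-5L difference.

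**ANCOVA against the ICER.** The model needs an outcome per participant and visit, a baseline covariate and a group-by-time term. The ICER is (difference in mean cost) / (difference in mean QALY), one value per trial. It supplies none of these. Costs, QALYs and EQ-5D-5L do exist per participant; their ratio of group differences does not.

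**Does 90% carry over to the QALY difference?** EQ-5D-5L is measured at 0, 8 and 16 weeks, so the trapezoid weights are 4/52, 8/52 and 4/52 year. Assumptions: SD 0.12, correlation 0.5 between visits (or between changes), 62 per group, gain building linearly to 0.07 at week 16.
- QALY difference = 0.07 × (0.5 × 8 + 4)/52 = 0.0108.
- Raw QALYs: SD = (0.12/52) × √176 = 0.0306; SE = 0.0306 × √(2/62) = 0.0055; power about 50%.
- Change from baseline, with 0.12 as the SD of change: SD = (0.12/52) × √112 = 0.0244; power about 69%.
- Raw QALYs adjusted for baseline EQ-5D-5L: SD = (0.12/52) × √(176 − 100) = 0.0201; power about 85%.
- If the full 0.07 is reached by week 8: QALY difference = 0.07 × 12/52 = 0.0162; with the change SD of 0.0244, power about 96%.

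The answer depends on trajectory, correlation and baseline adjustment, so no single figure should be quoted. For the ICER or net benefit no figure can be derived at all: the document gives no cost difference, cost SD, cost–QALY correlation or threshold.

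**The curve under a bare ICER-below-threshold count.** Assumptions, none from the document: threshold 20,000 per QALY, incremental cost 50 with SE 40, independent normal differences. The QALY SE of 0.0055 is the raw figure above. Net benefit = 20,000 × QALY difference − cost difference.

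True QALY effect zero, by quadrant:

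| Replicates | Share | ICER below threshold | Net benefit above 0 |
|---|---|---|---|
| More effective, dearer, ICER below threshold | 27.5% | counted | counted |
| More effective, cheaper (dominant) | 5.3% | counted | counted |
| Less effective, dearer (dominated) | 44.7% | counted | not counted |
| Less effective, cheaper, ICER below threshold | 4.6% | counted | not counted |
| Less effective, cheaper, ICER above threshold | 0.7% | not counted | counted |
| Total | | 82% | 33% |

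The remaining replicates are more effective and dearer with an ICER above the threshold, and neither rule counts them. Closed-form check: Φ(−50 / √((20,000 × 0.0055)² + 40²)) = Φ(−50/117) = 0.33.

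Other cases:
- Zero effect, cost 100, SE 60: 70% against 21%.
- Half the planned effect (0.0054), cost 50, SE 40: 85% against 69%.
- Planned effect (0.0108), cost 50, SE 40: about 95% against 92%.

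**The case against.** The strongest reply is that the plan already handles the ICER properly. It has its own bootstrap, plane and curve, so the primary outcome is not left without a method. Replicates can only be plotted on axes of cost difference and effect difference if each carries both differences, so the pairs are implied and ICER replications is loose shorthand. The authors name the quadrant that is less effective and more costly, so they recognise dominated results. A detailed classification rule is also something an article may leave to a fuller document.

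Most of this stands. A reader might infer that the plan counts dominated results as cost-effective; it does not say so, and an analyst using the plotted pairs would avoid the error. What remains is that the sentence names ratios as the input to the curve and nothing in the text excludes the faulty count.

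A reader might also infer that the plan claims 90% power for the ICER, or that true QALY power is only about 50%. Neither is supported. The Sample size section openly ties the power to the EQ-5D-5L change, and 50% is the low end of results that move widely with the assumptions.

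The reply does not reach the ANCOVA sentence. It covers the primary outcome explicitly and cannot be carried out; further detail elsewhere could only overrule it.

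**Conclusion.** The point holds in three limited parts.

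- **Definite:** the ANCOVA sentence prescribes an analysis that is impossible for the ICER and conflicts with the bootstrap given in the Cost-effectiveness analysis section. This rests on the text alone.
- **Ambiguity:** the rule for the acceptability curve is open, and the wording permits a count that mixes good and bad replicates. The possible error is large near a zero QALY effect (82% against 33%) and small at the planned effect (about 95% against 92%). These sizes rest on assumed costs, SE and threshold.
- **Scope:** the 90% power is correct for the EQ-5D-5L difference and should not be read as applying to the QALY difference or the ICER.

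**What to change.** 1. Limit the ANCOVA sentence to outcomes measured on participants, and refer the ICER to the Cost-effectiveness analysis section.
2. Keep the 1000 bootstrap pairs of cost difference and QALY difference. At each threshold over a stated range, compute incremental net monetary benefit = threshold × QALY difference − cost difference, and report it with a 95% CI.
3. Define the acceptability curve as the share of replicates with net benefit above 0.
4. Report the ICER as a point estimate, alongside the plane.
5. State that the 90% power refers to the EQ-5D-5L difference and not to the QALY difference or the ICER.

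Making EQ-5D-5L a primary effectiveness outcome would change the outcome hierarchy and is not needed to correct these points.

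The cost is some rewording and a few lines of analysis code, with no new data. The one downside is that the stated power becomes visibly narrower in scope.

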## Discussion

This paper describes the protocol for a RCT that aims to determine the clinical and cost-effectiveness of a primary care-based exercise intervention in perimenopausa women. Physical activity during the menopause transition and post menopause period has been reported to improve mental health, prevent weight gain, increase bone mineral density and muscle mass and reduce the risks of other diseases (e.g. cancer, diabetes, heart disease) [5, 65]. Additionally, increasing evidence suggests that exercise is a safe and useful strategy for alleviating menopause symptoms [65], with no serious reported side-effects [65]. For all those reasons, policy makers should consider encouraging general practitioners to prescribe exercise programs in primary care settings in collaboration with exercise specialists [66]. In Spain, the 2012 national health survey [67] revealed that 82 % of the population visited primary health care centres, making this an ideal setting for undertaking exercise intervention programs [68]. Most interventions to increase physical activity in primary care have been cost-effective [68]. A review showed the effectiveness of at least 12 months of primary care-based interventions to promote physical activity [69]. However, most of the interventions involved advice or counselling given face to face, or by phone (or both), and few trials have investigated supervised exercise interventions [69]. Further exercise interventions are needed, with objective outcome measures [69]. This project will be a primary care-based RCT and its results may potentially be generalizable to similar primary care settings. The designed intervention is also feasible and non-expensive. If the present RCT proves to be effective, it can be easily transferred to other similar contexts. Additionally, we will analyse the association of physical activity, sedentary behaviour and physical fitness with the other variables registered and with pharmacological and health service costs. Consequently, the findings of the FLAMENCO Project will help the health care system to identify preventive strategies for primary prevention and health promotion as well as strategies to reduce health care requirements and cost.

## Abbreviations

CVD: Cardiovascular disease
GDP: Gross domestic product
ICER: Incremental cost effectiveness ratio
QALY: Quality adjusted life years
RCT: Randomized controlled trial
RPE: Rate of perceived exertion
SF-36: Short-form health survey 36
